### Interim analyses {21b}

No interim analysis is planned in the current study.

### Methods for additional analyses (e.g., subgroup analyses) {20b}

No additional analyses are planned for the current study.

### Methods in analysis to handle protocol non-adherence and any statistical methods to handle missing data {20c}

Non-adherence will be handled through the use of intention to treat analysis in the primary analysis. Missing data will be handled by baseline observation carried forward in the primary analysis. Due to the randomised design, multivariable models will not be used to adjust for confounding, and therefore missing covariates will not impact the primary analysis.

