### Outcomes {12}

Baseline characteristics will be collected—age, sex, blood pressure, duration of diabetes, current medications, current comorbidities and blood lipids.

All outcomes measures will be assessed at baseline, 16 weeks and 32 weeks in all participants.

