#### Primary outcome measure

The primary outcome measure is change in HbA1c from baseline to 32 weeks.

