### Sample size {14}

Previous research has shown that resistance exercise training can result in an ~ 0.6% decrease in HbA1c [12], with a 0.5% in HbA1c also being classified as a clinically relevant change. To detect a 0.5% decrease in HbA1c (standard deviation within groups 0.79%) in the home-based group or gym group versus control, we would require 40 participants per group at 80% power at the 5% significance level. We will recruit 50 to each group to account for drop out.

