## Assignment of interventions: allocation

### Sequence generation {16a}

Following the baseline assessment, patients will be randomised to the home- or gym-based resistance exercise group or the control group (1:1:1 ratio) using a computer-generated randomisation sequence. Randomisation will be stratified by sex.

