## Statistical methods

### Statistical methods for primary and secondary outcomes {20a}

All statistical analyses will be carried out according to a detailed Statistical Analysis Plan, to be finalised prior to database lock. We will use an intention to treat approach for analysis, using baseline observation carried forward for those who do not attend the 16 weeks visit, and last observation carried forward at the 32 week visit. This will estimate the effect of the interventions. The primary (and secondary) outcomes (all continuous) will be analysed in a hierarchical fashion, first analysing the change in outcome in the gym-based group versus control at 16 weeks at 5% level of significance; this is the group we hypothesise will have the greatest effect size. If this first difference is found to be significant, the home-based group will also be compared to control at the 5% level, and if this is significant, the gym-based group will be compared to the home-based group at the 5% level. The overall type I error will not exceed 5% for each outcome because of the hierarchical nature of the testing. Comparison of the randomised groups at 32 weeks will be conducted in a similar fashion, as a secondary analysis, at the 5% level. As a secondary analysis, we will conduct a per protocol ‘completer’s analyses’ of those who attended at least the 16-week visits (irrespective of their protocol adherence or other characteristics after randomisation). This is a less conservative estimate of the effect of the intervention. Finally, in the per protocol group, we will also investigate the association and correlation of change in HbA1C with change in secondary outcomes.

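### Randomisation is given as the reason for using no multivariable models, but it answers confounding, not precision: the unadjusted change-score comparison is valid but less efficient than one adjusted for baseline HbA1c and sex

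*Protocol article*

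**What the plan says.** The section on non-adherence and missing data {20c} says "Due to the randomised design, multivariable models will not be used to adjust for confounding", and draws the consequence "and therefore missing covariates will not impact the primary analysis".

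The other relevant statements are:
- Primary outcome measure: "The primary outcome measure is change in HbA1c from baseline to 32 weeks".
- Statistical methods {20a}: "The primary (and secondary) outcomes (all continuous) will be analysed in a hierarchical fashion". The sequence begins by "first analysing the change in outcome in the gym-based group versus control at 16 weeks at 5% level of significance". No covariate is named there.
- Sequence generation {16a}: "Randomisation will be stratified by sex".
- Outcomes {12}: "All outcomes measures will be assessed at baseline, 16 weeks and 32 weeks in all participants". The Trial design section {8} places the baseline measurement before randomisation.
- Sample size {14}: the calculation is "To detect a 0.5% decrease in HbA1c (standard deviation within groups 0.79"%), with 40 per group needed for 80% power at the 5% level and 50 recruited to allow for drop-out.

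No section of the article provides for covariate adjustment.

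**The concern.** Randomisation removes systematic confounding, so no model is needed for that purpose. Adjusting for a prognostic baseline value does something else: it takes explained variation out of the residual and removes the effect of chance baseline differences. Adjusting for a stratification factor brings the standard error into line with the way patients were allocated. The stated reason addresses neither, so it does not support leaving these terms out.

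The benefit claimed in return, that missing covariates cannot matter, is close to empty for these two terms. Sex must be known in order to stratify, and HbA1c is measured in everyone before randomisation.

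What is at stake is power. It counts for more than usual here because testing is hierarchical: the home-based group is compared with control only if the gym-based comparison is significant, yet the home programme is what the Background and Discussion present as the open question. The point is the same whether the 16-week or the 32-week change is analysed.

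**Working it through.** **Inputs from the protocol article.** Difference 0.5%, within-group SD 0.79%, 40 per group, 80% power, 5% level, 50 recruited (Sample size {14}). Change from baseline is the analysed quantity (Primary outcome measure; Statistical methods {20a}). Baseline is carried forward for those who miss the 16-week visit ({20a}, {20c}).

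**Assumptions, not in the article.** The baseline to follow-up correlation rho is taken as 0.5 to 0.8. The variance s² is taken as equal at both times. The 0.79% is read as the SD of change; the article says only that it is within groups.

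**Step 1. Reproduce the stated size.** The two-sided normal formula is n = 2 × 0.79² × (1.960 + 0.842)² / 0.5² = 39.2, rounded up to 40. With the t distribution n is 40.2, and power at 40 per group is 79.8%. Then 40 / (1 − 0.20) = 50. The stated figure holds for an unadjusted, two-sided comparison.

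**Step 2. Variance with and without baseline as a covariate (complete data).**
- Change score: 2s²(1 − rho).
- Adjusted for baseline: s²(1 − rho²).
- Ratio: (1 + rho)/2, which is below 1 for every rho below 1.

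| rho | variance factor | residual SD from 0.79 | power at 40 per group (t) | n per group for 80% |
|---|---|---|---|---|
| unadjusted | 1 | 0.790 | 79.8% | 40.2 |
| 0.5 | 0.75 | 0.684 | 89.8% | 30.4 |
| 0.7 | 0.85 | 0.728 | 85.8% | 34.3 |
| 0.8 | 0.90 | 0.749 | 83.8% | 36.3 |

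The normal approximation gives 80.8% unadjusted, and 90.5%, 86.7% and 84.7% adjusted.

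**Step 3. Allow for baseline carried forward.** Let a fraction q have real follow-up and 1 − q have a change of exactly zero, at random and with no mean change.
- Variance of the imputed change: 2qs²(1 − rho).
- Its covariance with baseline: −qs²(1 − rho).
- Variance factor after adjustment: 1 − q(1 − rho)/2.

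With q = 0.8, the drop-out allowance implied by 40 and 50, the factor is 0.80, 0.88 and 0.92 at rho 0.5, 0.7 and 0.8. The variance reduction shrinks by one fifth (for example from 0.25 to 0.20). No power is quoted for this case, because carrying baseline forward also changes the mean difference.

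**Step 4. If 0.79% is the SD of a single measurement instead.** Power at 40 per group (normal approximation), change score versus adjusted: 66.7% versus 84.3% at rho 0.3; 80.8% versus 90.5% at rho 0.5; 95.5% versus 97.7% at rho 0.7. The direction is the same and the size varies widely.

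**Step 5. Sex.** A simulation used 40 per arm with sex perfectly balanced, an unadjusted t-test and a nominal 5% level. Type I error was 5.0%, 4.9%, 4.5% and 3.7% when sex explained an assumed 0%, 2%, 5% and 10% of the variance of the analysed outcome. Because change is what is analysed, that share means the part of the variance of change explained by sex.

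**The case against.** **The text may not exclude these terms.** Read literally, the sentence excludes models that adjust for confounding. It names neither baseline HbA1c nor sex, and a statistical analysis plan, not shown here, is still to be finalised. That is a fair caution. But the conclusion that missing covariates cannot affect the primary analysis holds only if no covariate enters it. The article therefore states a choice and does not merely leave a detail open.

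**Baseline is already used.** This stands. A reader might infer that baseline HbA1c is ignored altogether, but it is subtracted in the change score. What is forgone is only the factor (1 + rho)/2, which approaches 1 as rho rises.

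**The strength and body-composition outcomes.** A reader might infer that leaving out sex costs most for lean mass, grip strength, one-repetition maximum and push-ups, because these differ between men and women. The documents do not support this. Those are differences in level, and the plan analyses change, from which any stable sex difference is subtracted. Only a sex difference in change would matter, and the article gives no figure for one.

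**Chance imbalance as a second harm.** At 50 per arm, a 1-SD chance difference in baseline would move the unadjusted estimate by about 0.05% to 0.08% HbA1c (rho 0.8 to 0.5). It is tempting to add this to the power loss. It is the same variance seen from another side: 2(1 − rho) = (1 − rho²) + (1 − rho)², and the last term is the imbalance component.

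**The unadjusted analysis is sound.** This also stands, and it limits the weight of the point.

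**Conclusion.** The point holds as one of efficiency. The stated reason does not justify leaving out baseline HbA1c and sex as covariates, and including them would be a gain from data already in hand. Under the assumptions listed, the variance factor is 0.75 to 0.90 with complete data and about 0.80 to 0.92 with 20% of baselines carried forward at random. With complete data, power at 40 per group goes from about 80% to between 84% and 90%. The correlation and the meaning of the 0.79% are assumptions, and the gain is small if the correlation is close to 1.

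For sex, the cost is a mildly conservative test, confined to outcomes whose change depends on sex.

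The plan should not be read as biased or invalid. The unadjusted comparison is unbiased over randomisations, does not inflate type I error, and agrees with the stated sample size. The change is worth making, but the trial's validity does not depend on it.

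**What to change.** In section {20c}, and in the statistical analysis plan before database lock, replace the sentence on multivariable models with a prespecified model. Suggested content: each continuous outcome is analysed by a linear model (analysis of covariance or a repeated-measures equivalent) with arm, the baseline value of that outcome, and sex as terms. The unadjusted comparison of change is kept as a sensitivity analysis.

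The remark on missing covariates can then say that both covariates are collected before randomisation, so missing values should be rare. It would also help to state in the Sample size section whether 0.79% is the SD of change or of a single measurement.

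The cost is one sentence in each document. No new data are needed and the sample size need not change. Fixing the covariates now also avoids a decision to adjust after the data have been seen.

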### Plans to give access to the full protocol, participant level-data and statistical code {31c}

The data sets analysed and the codes used for these analyses are available from the corresponding author on reasonable request.

## Oversight and monitoring

### Composition of the coordinating Centre and trial steering committee {5d}

#### Principal investigator

Design and conduct of trialPreparation of protocol and revisionPreparation of study materials and case report formsOrganise steering committee meetingsPublication of study reports

#### Steering committee (see title page for members)

Agreement of final protocolAll lead investigators will be membersRecruitment of patients and liasing with principal investigatorsReviewing progress of study and if needed agreeing changes to protocol

#### Trial management committee (principal investigator, study coordinator, researchers)

Study planningAdverse event reportingResponsible for trial master fileBudget controlData verification

### Composition of the data monitoring committee, its role and reporting structure {21a}

Not applicable.

### Adverse event reporting and harms {22}

There are unlikely to be major safety issues with our proposed non-pharmacological interventions. However, if any safety concerns or incidents arise, we will follow our standard operating procedures for reporting adverse events in a non-Clinical Trial of an Investigational Medicinal Product (non-CTIMP) studies.

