**Methods:**

The current study is a three-arm randomised controlled trial which will be conducted with 150 eligible people with type 2 diabetes to compare home-and gym-based resistance exercise training with usual care in Kuwait. The interventions will be delivered by exercise specialists and last for 32 weeks. The primary outcomes are HbA1c with secondary outcomes measuring muscle function, body composition, physical activity and quality of life.

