#### Home-based resistance exercise

Participants assigned to the home-based resistance exercise group will be asked to perform exercises 3 times a week for the intervention period. Each session will begin with a 5-min warm-up and end with a 5-min cool-down, walking on the spot/stretching. Exercises will target all major muscle groups. The exercises will be press-ups, band lateral raises, band seated low row, squat, lunge, calf raise, and plank. The order of each session will be (1) squat, (2) press up, (3) calf raise, (4) band seated low row, (5) lunge, (6) band lateral raise and (7) plank. Where participants are unable to perform any of the exercises, suitable alternatives will be sought.

The first 3 sessions of the exercise will be performed, within our exercise facility, under the supervision of a qualified exercise specialist to ensure that the participants are comfortable with the exercises and are performing them appropriately. During these sessions, participants will perform 5–10 repetitions of each exercise (tiring but comfortably achievable). A similar session, within the gym facility, will take place at week 4 and then every 4 weeks of the study to overcome any issues with the exercises and to ensure progression to an appropriate intensity. In weeks 2–4, participants will perform, during each session, a single set of each exercise with this set performed to voluntary muscular failure—defined as not being able to perform another repetition. In weeks 5–8, this will progress to 2 sets of each exercise with both sets performed to voluntary muscular failure, in each session. In weeks 9–32, 3 sets of each exercise will be performed with all sets to voluntary muscular failure, in each session. When multiple sets (weeks 5 onwards) of each exercise are performed, these will be sequentially with 2 min rest between each set.

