#### Gym-based resistance exercise

Participants assigned to the gym-based resistance exercise group will undertake 3 supervised sessions per week. Each session will begin with a 5-min warm-up and end with a 5-min cool-down, walking or cycling and stretching. The exercises performed during each session will consist of leg press, calf press, leg curl, chest press, lateral raise, seated row, and plank. The order of the session will be (1) leg press, (2) chest press, (3) calf press, (4) seated row, (5) leg curl, (6) lateral raise and (7) plank. Where participants are unable to perform any of the exercises, suitable alternatives will be sought.

Exercises will be performed at 65–80% one repetition maximum (1RM), and this will be re-tested every 4 weeks of the intervention and the load adjusted accordingly. In week 1, participants will perform, during each session, a single set of 5–10 repetitions of each exercise (tiring but comfortably achievable) to ensure they are comfortable with the exercises and are performing these in the correct form. In weeks 2–4, participants will perform, during each session, a single set of each exercise with this set performed to voluntary muscular failure—defined as not being able to perform single another repetition. In weeks 5–8, this will progress to 2 sets of each exercise with both sets performed to voluntary muscular failure, in each session. In weeks 9–32, 3 sets of each exercise will be performed with all sets performed to voluntary muscular failure, in each session. When multiple sets (weeks 5 onwards) of each exercise are performed, these will be sequentially with 2 min rest between each set.

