### Strategies to improve adherence to interventions {11c}

For participants in the home-based group, the trainer will send a message to each participant on the day of their training session to remind them to carry out the exercise and to respond to say they have done it. An exercise log will also be provided for participants.

Those in the gym-based group will be sent a reminder message to ensure attendance at the supervised exercise sessions within our gym facility.

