## Discussion

The current trial is a single-centre, three-arm randomised controlled trail. It has been designed to test the effectiveness of home- and gym-based resistance exercise training over a period of 32 weeks in people with type 2 diabetes. It is known that resistance exercise training can effectively reduce HbA1c in people with type 2 diabetes [12] and the current study will answer whether delivery of such an intervention without regular supervision and outside of a gym-based facility is also effective, potentially allowing a more pragmatic delivery of resistance exercise within clinical practice.

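### Adverse-event handling is described only as reactive while supervised sessions number 96 (gym), 10 to 11 (home) and 0 (control), so harms reported by arm risk ascertainment bias unless all arms are asked the same scheduled questions

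*Protocol article*

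**What the plan says.** **Harms.** Under Adverse event reporting and harms {22}, the protocol article states "There are unlikely to be major safety issues with our proposed non-pharmacological interventions" and adds that "if any safety concerns or incidents arise, we will follow our standard operating procedures for reporting adverse events". Adverse event reporting is also listed among the trial management committee's duties. A data monitoring committee is marked as not applicable.

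**What every arm is measured on.** Outcomes {12} schedules all outcome measures at baseline, 16 weeks and 32 weeks for all participants. The primary outcome is HbA1c. The secondary list covers body composition, physical function, strength, activity, quality of life and current medications. It contains no adverse event or injury item.

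**Contact by arm.**
- Gym: "Participants assigned to the gym-based resistance exercise group will undertake 3 supervised sessions per week". The abstract's Methods say "The interventions will be delivered by exercise specialists and last for 32 weeks".
- Home: "Participants assigned to the home-based resistance exercise group will be asked to perform exercises 3 times a week for the intervention period". The first three sessions are supervised at the facility, and "A similar session, within the gym facility, will take place at week 4 and then every 4 weeks of the study". On training days the trainer messages participants "to remind them to carry out the exercise and to respond to say they have done it", and an exercise log is provided.
- Control: usual care, with no trial sessions.

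**Blinding.** Participants and research staff know the allocation. Only the analysis is to be blind.

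**The concern.** The stated trigger is that something arises, after which a reporting procedure applies. Nothing in the article says how an event becomes known. If it becomes known mainly through contact with trial staff, allocation decides how likely that is: a specialist sees gym participants three times a week, most home sessions are unobserved, and controls attend no sessions. The home arm's session reply, as described, concerns adherence and not harm.

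The Discussion says that "the current study will answer whether delivery of such an intervention without regular supervision and outside of a gym-based facility is also effective". That is a question about effectiveness, but anyone weighing the result for practice will also ask whether home training was as safe as gym training. Under-detection would favour the home programme in exactly that contrast. Against control the distortion runs the other way, because both exercise arms have more contact and so more opportunity for unrelated events to be noted. Blind analysis does not help, since events that were never recorded cannot be recovered later.

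**Working it through.** **The plan's own figure.** The article gives no harms figure and no total of supervised sessions, so there is nothing of that kind to reproduce. The planned 50 per group is used below only to turn proportions into counts.

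**Supervised sessions over 32 weeks** (inputs from the abstract's Methods and the two intervention descriptions)
- Gym: 3 per week × 32 weeks = 96.
- Home: 3 initial sessions + sessions at weeks 4, 8, …, 32 (32 / 4 = 8) = 11. If the week-32 session is not counted, 3 + 7 = 10.
- Control: 0.
- Home sessions planned: 3 × 32 = 96. Assuming the four-weekly sessions replace home sessions, 96 − 11 = 85 are unobserved (86 if only 10 are supervised).

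**Other contact.** Supervised sessions are not all the contact there is. The home arm also has up to about 96 message exchanges and a log. Every arm, control included, has the two post-baseline visits. Neither the messages nor the log is described as asking about harm, and no harm is listed among the measures at the shared visits.

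**How unequal detection would act.** Let the true risk p be the same in every arm and let d be an arm's probability that an event is recorded. The expected recorded count is 50 × p × d, so the apparent risk ratio between two arms is the ratio of their d values and p cancels. The document gives neither p nor d. With p = 0.20 assumed, there are 50 × 0.20 = 10 true events per arm. All d values below are assumptions.

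| d gym / home / control | Recorded gym / home / control | Home vs gym | Gym vs control | Home vs control |
|---|---|---|---|---|
| 0.9 / 0.9 / 0.9 | 9 / 9 / 9 | 1.00 | 1.0 | 1.00 |
| 0.9 / 0.7 / 0.5 | 9 / 7 / 5 | 0.78 | 1.8 | 1.40 |
| 0.9 / 0.5 / 0.3 | 9 / 5 / 3 | 0.56 | 3.0 | 1.67 |
| 0.9 / 0.3 / 0.2 | 9 / 3 / 2 | 0.33 | 4.5 | 1.50 |

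The table shows direction and mechanism only. With equal detection the distortion is nil. With detection ordered as the supervised sessions are, home looks safer than gym and both exercise arms look worse than control, with no true difference.

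**The case against.** The strongest reply is that the article defers to standard operating procedures that the reader cannot see. These may prescribe active, scheduled questioning, and a journal article commonly leaves such detail to them. This stands to the extent that nobody can say harms will in fact be collected passively. What the article does describe is procedures for reporting events once they have arisen, and it nowhere says that events are asked about.

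Several stronger readings are tempting, and the document does not support them:
- *Harms are recorded only if they happen to come to light.* The text is silent on detection. Passive detection is an inference from it.
- *Controls have no staff contact.* They attend at 16 and 32 weeks. The figures 96, 10 to 11 and 0 count supervised sessions only.
- *The shared visits do not collect harms.* Absence from the outcome list does not prove that nothing is asked there. It shows only that the article does not provide for it.
- *Any safety comparison is biased.* No between-arm safety comparison is planned in the objectives, outcomes or statistical methods. The risk attaches to harms if they are reported by arm. Serious events may surface whatever the contact.
- *Home training will look falsely safe.* This could apply against gym only. Against control, home training would look less safe.

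What remains is a reactive description, no harm item at the visits that all arms share, and observation that differs sharply by arm in an open-label trial.

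**Conclusion.** The point holds as a risk, not as a demonstrated bias. The supervised-session counts of 96, 10 to 11 and 0 are firm. Unless the unseen procedures already require the same active questioning in every arm, harms reported by arm are open to ascertainment bias, with home favoured over gym and both exercise arms disadvantaged against control. This direction assumes that detection rises with supervised contact. The size cannot be derived from the document. The primary HbA1c analysis is unaffected. It is a worthwhile, inexpensive improvement that has to be made during data collection, because it cannot be repaired at analysis.

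**What to change.** 1. At the existing 16- and 32-week visits, ask all three arms one identical set of adverse-event questions, with the same wording and the same recall period (since the last scheduled visit).
2. Use those answers for harms reported by arm, and say so in the harms section.
3. Tabulate separately, by source, any event learned only through arm-specific contact: supervised sessions, home messages or the home log.
4. If a harm question is added to the home-arm message, do not use its answers for between-arm comparison, because it would be a detection channel that only one arm has.
5. If the standard operating procedures already require equal active questioning, one sentence saying so in the harms section settles the point.

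The cost is about one form page at two visits that already take place, and one additional table. The downsides are slightly longer visits and reliance on recall over 16 weeks, which may lose minor events. That loss should be more nearly alike across arms than detection through contact, although participants still know their allocation.
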